#### CFU measurements:

A 1-cm section of the catheter is washed 3 times with saline. Transfer each section to 2 ml of saline 0.9% and sonicate for 20 seconds (30KHz). CFU's are determined by plating each sample on blood agar after serial dilution with saline and incubation at 37°C overnight.

## **11.4 Safety Parameters**

### **11.4.1 Adverse Events**

Adverse events will be recorded from the date of patients signed informed consent form and throughout the study, including the follow-up period. They should be reviewed and updated at each subsequent visit and during any phone contact with the patient.

### **11.4.2 Potential Adverse Events Related to NO-impregnated Catheters**

- Bleeding (i.e hemoptysis)
- Decrease in blood pressure
- Erection
- Local irritation

(See appendix 5 - table of possible adverse events related to NO-impregnated catheters).

**11.4.3 Safety Laboratory Evaluations**

Bleeding test such as prothrombine time (PT), international normalized ratio (INR), activated partial thromboplastin time (aPTT) will be performed (see section 8)

## 12. SAFETY

Any untoward event that occurs, whether or not the investigator considers the event to be related to the use of the NO-impregnated catheters, and any new condition or worsening of a pre-existing condition will be considered an AE. Stable chronic conditions that are present prior to study entry and do not worsen during the study will not be considered AEs.

An abnormal result of diagnostic procedures, including abnormal laboratory findings, will be considered an AE if it:

- Results in patient's withdrawal by the investigator
- Is associated with a SAE
- Is associated with clinical signs or symptoms
- Is considered by the physician to be of clinical significance

The intensity or severity of the AE will be characterized as:

Mild: AE which is easily tolerated

Moderate: AE sufficiently discomforting to interfere with daily activity

Severe: AE which prevents normal daily activities.

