## 5. STUDY END POINTS

### 5.1 Primary End Point(s)

#### **Safety:**

- Determine AEs and SAEs associated with NO-impregnated catheters
- Proportion of patients (%) who prematurely discontinued the study due to AEs or SAEs

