#### 7.5.1 Criteria for Treatment Discontinuation

- AEs that are suspected to be related to NO-impregnated catheters, according to physician discretion

- Blood pressure and heart rate above or below the 20% of the normal ranges for the patient baseline

A patient whose treatment was discontinued for any reason should complete all study assessment including the follow up visits.

Concomitant medication (i.e. antibiotics) given during the study will not be a reason for treatment early discontinuation.

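### A catheter stopped under the blood-pressure/heart-rate criterion in a patient kept in the study does not enter the primary discontinuation proportions as worded, and its recording as an AE can rest on open-label judgement

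*Protocol*

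**What the plan says.** Section 7.5.1 gives two separate grounds for stopping catheter treatment. One is an AE suspected to be related to the device. The other is numeric: "Blood pressure and heart rate above or below the 20% of the normal ranges for the patient baseline". The second requires neither an AE nor a symptom. The section then adds: "A patient whose treatment was discontinued for any reason should complete all study assessment including the follow up visits". Withdrawal from the study has its own list in 7.5.2, and blood pressure and heart rate are not on it.

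Section 12 opens with a broad definition of an AE: "Any untoward event that occurs, whether or not the investigator considers the event to be related to the use of the NO-impregnated catheters". It then sets a narrower rule: "An abnormal result of diagnostic procedures, including abnormal laboratory findings, will be considered an AE if it" meets one of four conditions. These are "Results in patient's withdrawal by the investigator", association with an SAE, "Is associated with clinical signs or symptoms", and "Is considered by the physician to be of clinical significance". Stopping treatment or removing the catheter is not among them.

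Section 5.1 has three primary endpoints. The first is AEs and SAEs associated with the NO catheter. The second is "Proportion of patients (%) who prematurely discontinued the study due to AEs or SAEs". The third, for tolerability, is the same proportion restricted to events associated with the NO catheter. The synopsis repeats them.

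**The concern.** The trial exists to describe safety and tolerability. A fall in blood pressure is a named possible effect of the device (11.4.2 and Appendix 5), and blood pressure and heart rate are recorded every 8 hours in hospital (5.3.1). A patient whose catheter is taken out under the protocol's own haemodynamic criterion is the kind of patient a reader would expect to find in the primary results.

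The wording does not secure this. Stopping treatment and leaving the study are separate events in 7.5.1 and 7.5.2, and the discontinuation endpoints count only the second. The remaining endpoint needs the event to be recorded as an AE and attributed to the catheter. The design is open label, so where recording depends on clinical significance, the person deciding knows which catheter was used.

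**Working it through.** The plan states no figure on this point, so there is none to reproduce. The check follows one patient through the text and then sizes the effect of one case.

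**The case.** An NO patient's blood pressure or heart rate meets the 7.5.1 criterion without symptoms or an SAE. The catheter is removed and not replaced. The patient attends every remaining visit, as 7.5.1 directs.

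**Is it an AE under the section 12 list?**
- Withdrawal by the investigator: no, because the patient stays in the study.
- Association with an SAE: no.
- Clinical signs or symptoms: there are no symptoms. Whether the excursion is itself a sign is not stated.
- Clinical significance: the physician decides.
- The general definition at the head of section 12 may also apply, since the list does not say that vital signs are diagnostic procedures.

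The answer is therefore not fixed, and the only listed condition that clearly remains open is a judgement.

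**Does it reach a primary endpoint in 5.1?**
- AEs and SAEs associated with the NO catheter: only if it is recorded as an AE and judged to be associated.
- Study discontinuation due to an AE or SAE: no, even if it is recorded as an AE, because the patient has not left the study.
- Study discontinuation due to a device-associated AE or SAE: no, for the same reason.

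Two of the three endpoints miss the case however the AE question is settled. The first depends on that question and on causality.

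**Where other sections pull the other way.** Section 6.1 treats a patient as having completed the study once treatment is completed, and the per-protocol definition in 13.3 equates the two. Section 7.5 is headed as treatment discontinuation but speaks of patients leaving the study. Section 8.6 deals with early catheter removal under study discontinuation. Section 7.5.2 allows, but does not require, withdrawal when a catheter must be replaced. If these sections were followed instead of 7.5.1, the same patient could count as a study discontinuation.

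**Size of one case.** Inputs: n = 6 NO patients (6.1) and a 95% CI for the discontinuation proportions (section 13). The interval method is not named, so the exact Clopper-Pearson interval is assumed.
- Not counted, 0/6 = 0%. Upper limit 1 − 0.025^(1/6) = 0.459. Interval 0 to 45.9%.
- Counted, 1/6 = 16.7%. Lower limit 1 − 0.975^(1/6) = 0.0042. The upper limit solves (1 − p)^6 + 6p(1 − p)^5 = 0.025, giving p = 0.641. Interval 0.4 to 64.1%.

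**How likely is at least one case?** The documents give no excursion rate. With an assumed per-patient probability q, the chance of at least one among six is 1 − (1 − q)^6:
- q = 5%: 26%
- q = 10%: 47%
- q = 20%: 74%
- q = 30%: 88%

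**The case against.** A reader might infer that section 12 rules out as an AE any finding that leads to catheter removal, so that such a case can count nowhere. The text does not say that. The list is silent on removal; it does not exclude it. The general definition is broad. The third condition covers signs as well as symptoms, and the protocol calls blood pressure and heart rate vital signs. Vital signs are also assessed and analysed apart from laboratory tests (11.2, 11.3 and 13.4), so the narrower list may not govern them. A fall in blood pressure is itself a listed potential AE. What remains is mainly a symptom-free rise in blood pressure or a change in heart rate that the physician does not consider clinically significant, although the catheter was stopped for it.

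It is also fair to say that the data would not be lost. All variables are listed individually, clinically notable vital signs and shifts from baseline are tabulated by group, and reasons for discontinuation go on the CRF. With 12 patients, a single case would be visible. Unblinded judgement comes with the declared open-label design, and the study claims no power.

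These points narrow the AE part of the concern. They do not answer the endpoint part: under 7.5.1 the patient stays in the study, and 5.1 counts only those who leave it. The sections that blur the two do not close the gap. They make the same event countable or not, depending on which section the analyst follows.

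**Conclusion.** The point holds in a limited form. A catheter stopped under the blood-pressure/heart-rate criterion in a patient retained as 7.5.1 directs is outside both primary discontinuation proportions as worded. Whether it appears in the primary AE count can rest on open-label physician judgement about clinical significance and association with the device. The uncertainty over AE recording is clearest for a symptom-free rise in blood pressure or a change in heart rate.

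The documents do not support the stronger claim that such a case is barred from being an AE or must be absent from every primary endpoint. Nor do they support saying that an edit to section 12 alone would move the primary proportion. Relabelling the event as an AE adds nothing to a count of patients who left the study.

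The difference between 1/6 (16.7%, 0.4 to 64.1%) and 0/6 (0 to 45.9%) therefore arises only if 5.1 also counts treatment discontinuation. It assumes one case and exact intervals. It illustrates scale and does not predict a result. The change is worth making because safety and tolerability are the trial's only primary objectives and the correction is small.

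**What to change.** 1. In section 12, extend the first condition on the abnormal-result list so that it also covers discontinuation of study treatment under 7.5.1, in both arms. State that the list applies to vital signs, since otherwise the added words may not reach this case.
2. In 5.1 and the synopsis, define the discontinuation endpoints as premature discontinuation of study treatment or of the study due to AEs or SAEs. Carry the same wording into the tolerability analysis in 13.4.
3. Reconcile 6.1, 7.5, 7.5.1, 7.5.2, 8.6 and 13.3 on whether stopping the catheter is study discontinuation.

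No change to the blood-pressure/heart-rate criterion is proposed. The cost is a few lines of protocol text, a matching line in the CRF guide, and possibly a less favourable AE or discontinuation count.

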### **The causality of the AE will be assessed as:**

**Unrelated:** when the AE is clearly and incontrovertibly due to extraneous causes (disease, environment, etc.).

**Unlikely related:** if the AE meets at least two of the following criteria: 1) it does not follow a reasonable temporal sequence from catheterization; 2) it could readily have been produced by the patient's clinical state, environmental or toxic factors, or other modes of therapy administered to the patient; 3) it does not follow a known pattern of response NO.

**Possibly related:** if the AE meets at least two of the following criteria: 1) it follows a reasonable temporal sequence from catheterization; 2) a causal relationship to the experimental treatment cannot necessarily be reasonably excluded and an alternative explanation (e.g., concomitant drug or concomitant disease) cannot be reasonably suggested as causing the SAE; 3) it follows a known pattern of response to NO.

**Probably related:** if the AE meets at least three of the following criteria: 1) it follows a reasonable temporal sequence from catheterization; 2) it cannot be reasonably explained by the known characteristics of the patient's clinical state, environmental or toxic factors, or other modes of therapy administered to the patient; 3) it disappears or decreases on catheter removal, and it follows a known pattern of response to NO.

The date of onset, a description of the AE, severity, seriousness, action taken, relationship to the NO-impregnated catheter, outcome of the event, and date of resolution will be recorded. It should be documented if considered an SAE.

An SAE is defined as an AE that

- Results in death
- Is life-threatening
- Requires re-hospitalization or prolongs existing inpatient hospitalization
- Results in persistent or significant disability or incapacity
- Is an significant medical event which requires medical intervention to prevent any of the above outcomes

**Significant medical events** are those that may not be immediately life-threatening, but may jeopardize the patient and may require intervention to prevent one of the other serious outcomes listed above. Occurrences resulting in an AE will normally be considered serious by this criterion.

Inpatient hospitalization, or prolongation of existing hospitalization, mean that hospital inpatient admission and/or prolongation of hospital stay were required for treatment of AE, or that they occurred as a consequence of the event. It does not refer to pre-planned elective hospital admissions for treatment of a pre-existing condition that has not significantly worsened, or to any diagnostic procedure.

Any new SAE that occurs after the study period and is considered to be related (possibly/probably) to the study participation should be recorded and reported immediately, as requested by the Israeli Ministry of Health (MOH).

In order to satisfy regulatory requirements, any SAE, whether deemed IP-related or not, must be reported to the sponsor and to the study monitor as soon as possible after the investigator or coordinator has become aware of its occurrence. The SAE form completion and reporting must not be delayed even if all of the information is not available at the time of the initial contact.

The SAE should be submitted to the sponsor within 24 hours of becoming aware of the event. Additional information (follow-up) about any SAE unavailable at the initial reporting should be forwarded by the site to the sponsor within 24 hours of the information becoming available.

The SAE report (initial and/or follow-up) should be sent via e-mail to:

[contact]

AND faxed to fax number: [[name]]([contact])

The e-mail or the fax confirmation should be filed in the Investigator Site File.

The SAE will be reported to the regulatory authorities (CA) and EC/IRBs, according to Israeli Ministry of Health regulations (MoH form 13 or the SAE report form can be used, as requested by the IRB).

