### **7.5.2 Criteria for Early Study Withdrawal**

A patient may withdraw or be withdrawn from the study for the following reasons:

- 1) Patient withdrew consent.
- 2) Protocol violation/ non-compliance.
- 3) Loss to follow-up/failure to return.
- 4) Patient with difficulty in insertion of catheter during surgery.
- 5) In cases which require catheter replacement.
- 6) Serious adverse event

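### One sentence in the SAE definition makes seriousness the default for adverse events, contradicting the protocol's own five SAE criteria

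*Protocol*

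**What the plan says.** Section 12 of the protocol builds the safety vocabulary in steps.

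- **AE.** The definition is broad: "Any untoward event that occurs, whether or not the investigator considers the event to be related to the use of the NO-impregnated catheters", together with new or worsened conditions. The lowest severity grade is "Mild: AE which is easily tolerated".
- **SAE.** An AE is serious if it meets one of five criteria: death, threat to life, re-hospitalisation or a longer stay, lasting or significant disability, or the fifth, "Is an significant medical event which requires medical intervention to prevent any of the above outcomes".
- **Explanation of the fifth criterion.** Such events need not be immediately life-threatening but "may jeopardize the patient and may require intervention to prevent one of the other serious outcomes listed above". The paragraph then closes with "Occurrences resulting in an AE will normally be considered serious by this criterion".
- **Recording.** Severity and seriousness are separate items for each AE, and "It should be documented if considered an SAE". Section 11.2 likewise has the CRF record whether each event is regarded as an SAE.
- **Reporting.** "The SAE should be submitted to the sponsor within 24 hours of becoming aware of the event". This applies whether or not the event is thought related to the product.

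Other sections use the label. Section 5.1 names AEs and SAEs as the primary safety endpoint, along with the proportion of patients who discontinue because of either. Section 7.5.2 includes "Serious adverse event" among the reasons for which a patient may leave the study. Section 13.4 tabulates AEs and lists SAEs individually with their seriousness criteria.

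**The concern.** The fifth criterion is meant to catch a limited group: events that meet none of the first four criteria but could lead to one of those outcomes without intervention. Its closing sentence replaces that test with the mere occurrence of an AE. Every AE is an occurrence that results in an AE, so the sentence, read literally, sets no threshold.

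This is a first-in-human device study whose primary objective is safety and tolerability, with six patients per group. Its main result will be a short account of which events occurred and which were serious. If the definition can be read two ways, the same mild event may be coded serious for one patient and non-serious for another, and a reader of the report cannot tell which rule was used. The label also has operational effects: a 24-hour report, follow-up of the SAE until it resolves, stabilises or is explained, and eligibility for withdrawal under Section 7.5.2.

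**Working it through.** No figure in the protocol depends on this sentence, so the check sets the passages against each other.

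**1. Scope of the sentence.** An AE in Section 12 is any untoward event, related or not, and may be mild. The disputed sentence makes occurrences that result in an AE normally serious. Together these make serious the default class and non-serious the exception.

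**2. Conflict with the rest of the protocol.**

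| Place | What it implies | Consistent with the sentence? |
|---|---|---|
| Section 12, five SAE criteria | SAEs are the subset of AEs that meet a stated criterion | No; the list would have little left to do |
| Section 12 and Section 11.2, recording | Seriousness is decided event by event, apart from severity | No; the answer would normally be yes |
| Section 13.4 | AEs are tabulated; SAEs are listed with the criterion met | No; the criterion would often be only that an AE occurred |
| Appendix 5 | Local irritation is a foreseeable AE, while life-threatening, hospital-stay-prolonging, disabling or fatal events are not expected | No; mild irritation would normally be serious |

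No other passage narrows or corrects the sentence.

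**3. Where the label leads.**

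- *Reporting.* Every SAE, related or not, goes to the sponsor within 24 hours, so a minor event labelled serious goes with it.
- *Withdrawal.* Section 7.5.2 lists SAEs but not non-serious AEs. Section 7.5.1 covers AEs suspected to be related to the NO-impregnated catheter, and only for stopping treatment. Relabelling an unrelated minor AE therefore adds a ground for study withdrawal that it would not otherwise have. The list is permissive.

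**4. Effect on the discontinuation endpoints.** Take one arm of n = 6 treated patients, of whom d discontinue because of an AE or an SAE. The endpoint in Section 5.1 is d/6.

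- If an AE is relabelled an SAE and nobody's participation changes, d is unchanged. Change = (d − d)/6 = 0.
- If the relabelling leads an investigator to withdraw one more patient, the endpoint is (d + 1)/6. Change = 1/6 = 16.7 percentage points.

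The same holds for the tolerability endpoint in Section 5.1, which also pools AEs and SAEs but counts only those associated with the NO-impregnated catheter. An added withdrawal would also matter because Section 7.5.4 caps recruitment at 12 while asking for 6 + 6 completers, which leaves 12 − (6 + 6) = 0 spare.

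**The case against.** The strongest reply is that nobody would apply the sentence literally. The operative definition makes an SAE an AE that meets one of five criteria. The disputed sentence is softened by the word normally and tied to the criterion just before it. Section 13.4 requires each listed SAE to carry its seriousness criterion. The sentence is probably a drafting slip, and any error it causes runs towards over-reporting.

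Much of this stands. It limits the consequences, and three stronger readings that a reader might infer are not supported:

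- *That SAE proportions would approach 6/6 in both groups.* The protocol gives no AE frequency, the wording leaves the investigator some discretion, and no SAE rate is named as an endpoint.
- *That withdrawals due to SAEs would be inflated by definition.* Section 7.5.2 permits withdrawal and does not require it. The endpoints pool AEs with SAEs, so a change of label leaves the count as it was.
- *That genuine SAEs would be lost among minor ones, so severity and seriousness need separate tables.* With 12 patients, individual discussion of SAEs and AE tables by maximal severity, Section 13.4 largely covers this already.

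The reply does not remove the contradiction. The sentence is part of the definition that sites must apply, and falling back on the five criteria means disregarding what it says.

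**Conclusion.** The sentence is wrong as written and should be corrected. It contradicts the five SAE criteria in its own section and the separate recording of seriousness in Sections 11.2, 12 and 13.4. Until it is removed or reconciled, the AE/SAE split in the primary safety endpoint and the SAE listings is unreliable. Minor events can be sent into 24-hour reporting and become a permitted reason for withdrawal.

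The size is bounded rather than estimated. How many events would be misclassified depends on the AE frequency and on how investigators read the sentence, neither of which the protocol gives. For the pooled discontinuation proportions the direct effect is zero; any indirect effect is 16.7 percentage points per added withdrawal, assuming six treated patients in the arm.

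**What to change.** Delete the closing sentence of the significant-medical-event paragraph in Section 12. Alternatively, reconcile it with the fifth criterion by stating that an AE is serious only if it meets one of the five listed criteria, and not merely because it occurred.

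Keep the existing explanation that such events "may jeopardize the patient and may require intervention to prevent one of the other serious outcomes listed above". Limiting the criterion to cases where intervention was in fact needed would narrow it, which this correction does not call for.

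Align the CRF instruction for the seriousness field, and check that the use of the SAE label in Section 7.5.2 and in the Section 12 reporting rules is consistent with the corrected definition.

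The cost is one sentence in the protocol and one matching CRF instruction, handled as an amendment under Section 14.4 if the protocol is already approved. Sample size, visits and analyses do not change.
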